### Sample size and statistical analysis(es) :

### We plan to enroll 108 total subjects in the study, with 18 randomized to each arm. We will target this number with the understanding that minor attrition may occur, and estimate that we need 15 subjects per arm to complete the study to achieve our goals.

**Randomization Methods**: Randomization will be done after patch-testing results are read, to ensure that no subjects meeting exclusion criteria are involved in the study intervention. A researcher who does not interact directly with subjects will perform randomization. Subjects will be numbered (1-108). 18 subjects will be assigned to each group. A random number generated will be used to generate 18 numbers between 1 and 108. These subjects will be assigned to the first intervention group. Random number generation will be repeated in this way five times, with subjects corresponding to the number assigned to the treatment group for the round. The 18 remaining subjects will be assigned to the last treatment group.

**Blinding**: Researchers assessing HECSI scores for the hand exam and applying and interpreting results of the patch testing will be blinded to subject treatment group. Daily surveys will not record treatment arm and subjects will be instructed not to identify their group to examiners.

It is not possible to blind subjects to treatment, because the difference between soap and water, hand sanitizer, and chlorine solutions are obvious and cannot be obscured. However subjects assigned to one of the chlorine solution treatment groups will not be told which solution they have been assigned.

**Sample Size Calculations:** Because there are no previous handwashing studies using chlorine, soap, or hand sanitizer for handwashing that can provide information on the number of subjects likely to develop dermatitis we are unable to calculate a meaningful sample size for statistical significance. We feel that this small sample size is appropriate for a first study. For example if 20-100% of participants in a given arm develop dermatitis that will suggest that the method is problematic and should not be recommended, but if 0% of participants develop dermatitis this will be good evidence that the method has potential and should be studied further. This study is intended to be a first investigation that can provide information that could be used in the future for sample size calculations for a larger trial if any of the handwashing materials show potential.

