However this evidence on the impact of these substances on skin relies heavily on observational studies in environments that contain many other irritants1,4,9,10, or on studies of accidental exposure to higher levels of substances than is recommended for handwashing. Studies focused on workers in health care and other occupational settings experiencing irritants within their usual context and are not adequately able to separate the effect of handwashing substances from the environment. Indeed studies have shown that there are numerous factors including weather and baseline reactivity to substances that impact dermatitis1. Other studies focus on the potential for these substances to induce an irritant reactions, but not within a concentration and protocol accepted for handwashing3,5,6. This study will examine the impact of these substances when used appropriately for handwashing in a context where other potential irritants are carefully controlled and tracked to provide high quality evidence on the direct impact of these substances.

|  | **NaDCC** | **HTH** | **NaOCl (Stabilized)** | **NaOCl (Unstabilized)** |
| --- | --- | --- | --- | --- |
| *Original Product Form* | Powder or Tablets | Powder or Tablets | Liquid | Liquid |
| *Chemical Structure* | [figure not shown] | [figure not shown] | [figure not shown] | [figure not shown] |
| *Added Compounds* | 98% Pure (No added compounds) | Compounds to: prevent powdering, prevent absorption of moisture, or help tablet dissolve | Stabilizers (NaOH), Surfactants, Sud suppresors | None |
| *pH* | 6-7 | 10.4 – 10.8 | 10.8-11.4 | ~7 |

*Table 1. Summary of Chlorine Solutions*

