*Endline*: Endline data collection will occur on the last day of the intervention. All subjects will respond to the daily questionnaire and receive a hand exam as usual, and patch testing will be applied a second time according to the same protocol used during baseline. As during the previous assessment, subjects will remove the patch, mark the area, and take pictures after 48 and 96 hours and the area will be examined in person by a researcher on Day 7. Any suspected positive cases will be referred to [name] for verification and subjects with a confirmed positive will be recommended to avoid the substance in the future.

*Data Analysis*: As a preliminary study, the analysis for this study will be descriptive and foundational for further studies examining substances that show promise. The primary outcome of this study is the development of dermatitis, as measured by both HECSI score and self-perception index where subjects are asked to describe symptoms and discomfort experienced on a scale from 1-10. The HECSI score is a highly sensitive tool designed for use in research and epidemiological studies, and will serve as the gold standard of measurement for clinical dermatitis. However perception and discomfort are highly important aspects of the impact of dermatitis on patients, meaning the self-perception index adds an important dimension to the measurement of dermatitis as an outcome. We plan to compare the proportion of subjects presenting with signs and symptoms of dermatitis in each treatment group, and to stratify the results by gender and history of atopy in order to control for potential confounders.

[figure not shown]

*Figure 2. Study Timeline*

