### Subject Timeline: Subjects will be enrolled during a four week recruitment period during which informed consent will be collected. Subjects will be enrolled in the study for 7 weeks total, 4 of which will consist of daily intervention.

*Week 1*: Subjects will respond to the baseline survey, receive a hand exam, and have the baseline patch testing kit applied. After 48 hours, they will remove the patch and take a photo of the area. Subjects will take another photo after 96 hours and will be instructed to report any redness, bumps, or scaling at the patch site.

*Week 2*: On day 7 after patch testing subjects will receive an in-person examination of the patch test area. Any subjects meeting the exclusion criteria on the basis of the baseline survey, hand exam, or patch testing data will be excluded from the sample. After any subjects meeting exclusion criteria are removed from the sample, subjects will be randomized into one of the six treatment groups.

*Week 3 (Intervention Week 1)*: Week 3 is the first week of the intervention. Subjects will receive an orientation in handwashing procedures for their assigned treatment group and will wash their hands 10x daily with the substance assigned to their treatment group. Subjects will report daily to pick up handwashing materials for the next day and answer a short survey about compliance and hand feel, including a hand exam and photos of hands.

*Week 4 (Intervention Week 2)*: Week 4 is the second week of the intervention. Subjects will wash their hands 10x daily with the substance assigned to their treatment group, and will report daily to pick up handwashing materials for the next day and answer a short survey about compliance and hand feel, including a hand exam and photos of hands.

*Week 5 (Intervention Week 3)*: Week 5 is the third week of the intervention. Subjects will wash their hands 10x daily with the substance assigned to their treatment group, and will report daily to pick up handwashing materials for the next day and answer a short survey about compliance and hand feel, including a hand exam and photos of hands.

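### The fixed 1-to-108 draw has no rule for fewer than 108 eligible subjects, miscounts its own rounds, and leaves history of atopy and gender unbalanced

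*Protocol*

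**What the plan says.** Under *Sample size and statistical analysis(es)* the protocol states: "We plan to enroll 108 total subjects in the study, with 18 randomized to each arm". It expects some attrition and goes on to "estimate that we need 15 subjects per arm to complete the study to achieve our goals".

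*Randomization Methods* numbers the subjects 1 to 108 and describes the first round: "A random number generated will be used to generate 18 numbers between 1 and 108". These subjects form the first group. The draw is then to be repeated five times, after which "The 18 remaining subjects will be assigned to the last treatment group".

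Allocation comes after patch-test reading, and *Subject Timeline*, Week 2, confirms the order: "After any subjects meeting exclusion criteria are removed from the sample, subjects will be randomized into one of the six treatment groups". Under *Screening Interview/questionnaire*, the screening questions are asked only after consent.

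The baseline questionnaire records atopic disposition along with demographic information (*Baseline Assessment and Exclusion Criteria*). *Data Analysis* plans to compare the proportion with dermatitis across the groups and "to stratify the results by gender and history of atopy in order to control for potential confounders". Neither factor is used in the allocation.

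**The concern.** The procedure is written for one number of subjects. Between consent and randomisation, people can be lost to the hand exam, patch tests for six substances, history of dermatitis, occupation and pregnancy. Recruitment lasts four weeks, and the protocol gives no over-enrolment or replacement rule. If some of the 108 numbers have no subject behind them, arm sizes become unequal in a way that the text does not control, and the allowance of three losses per arm (18 − 15) may be used up before the intervention starts.

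The text also does not give one executable count of rounds.

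Finally, two factors that the analysis treats as potential confounders are known before allocation but left to chance. With 18 per arm, chance can put noticeably more atopic subjects in one arm than in another, and later stratification then has thin cells to work with.

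**Working it through.** **The plan's own figures.** 6 × 18 = 108, and 15/(1 − 3/18) = 18, so the totals agree. There is no power calculation to reproduce.

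**Count of rounds.** One draw plus five repetitions is six draws: 6 × 18 = 108, remainder 0. Five draws in all give 5 × 18 = 90, remainder 18. Only the second fits the sentence about the last group. Drawing without replacement is not stated either, though the remainder implies it.

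**Arm sizes with N eligible subjects (N is an assumption).** Suppose the draw covers 1 to 108 and the 108 − N empty numbers fall at random. Arm sizes x₁ to x₆ then follow a multivariate hypergeometric distribution, with probability ∏C(18, xᵢ)/C(108, N) and Σxᵢ = N. An arm can start below 15 only if it holds at least four empty numbers, so the probability is zero for N ≥ 105. At N = 104 all four must fall in one arm: 6 × C(18,4)/C(108,4) = 6 × 3,060/5,359,095 = 0.0034. Summing the same distribution exactly for other N:

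| N eligible | P(at least one arm < 15) | Mean smallest arm | Sets of six, no strata: smallest arm |
|---|---|---|---|
| 105 | 0 | 16.5 | 17 |
| 104 | 0.3% | 16.2 | 17 |
| 102 | 4.1% | 15.6 | 17 |
| 100 | 15% | 15.2 | 16 |
| 98 | 35% | 14.7 | 16 |
| 96 | 60.5% | 14.2 | 16 |

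The last column is the whole-number part of N/6. If five arms were instead filled with 18 existing subjects each, the last arm would get N − 90: 14 at 104, 10 at 100, 6 at 96. The text does not say which of these applies.

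**Atopy imbalance with a full 108 (prevalence is an assumption).** With K atopic subjects, their counts per arm follow the same distribution with K in place of N.

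| Prevalence | K | Mean gap, highest minus lowest arm | P(gap ≥ 5 of 18) | P(a given pair of arms differs by ≥ 4) |
|---|---|---|---|---|
| 10% | 11 | 3.2 | 10% | 5% |
| 20% | 22 | 4.3 | 42% | 15% |
| 30% | 32 | 4.9 | 57% | 20% |
| 40% | 43 | 5.2 | 64% | 24% |

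At 30%, some arm has three or fewer atopic subjects in 71% of draws. For scale, *Sample Size Calculations* regards 20% or more with dermatitis in an arm as a sign of a problem. In an arm of 18 that is 0.20 × 18 = 3.6, so four subjects. The effect of atopy on dermatitis is not given, so these gaps cannot be converted into a difference in the outcome.

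**The alternative.** List the atopic subjects first, then the others, and deal the whole list in randomly permuted sets of six without restarting between strata. Only the last set can be incomplete, so arm totals differ by at most one. The atopic subjects occupy the first K places, that is, complete sets plus at most one partial set, so their counts also differ by at most one. A simulation of 20,000 allocations, with N from 90 to 108 and K from 5 to 50, found no larger difference in either.

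**The case against.** The protocol can be read as already meaning 108 randomised subjects: it speaks of 18 randomised per arm, places the numbering after patch-test reading, and says that exclusions are assessed at enrolment. On that reading intake simply continues to 108. This is a fair reading, but the order in Week 2 leaves it open, and no reading says what happens if four weeks do not yield 108.

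The probabilities depend on a shortfall that the documents do not give, and they are negligible at 104 or more. That stands, and it is why a range is shown. An arm of 6 would require a researcher who knows that 96 are eligible to fill five arms with 18 regardless, against the evident aim of equal groups. It is a gap in the text, not a forecast.

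A draw to equal arms without stratification is valid, the study is descriptive, and stratified results are planned. The gap across six arms is an extreme statistic, and a given pair differs by four or more far less often. All of this stands. Lack of stratification is a weakness here, not an error.

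Four stronger readings are tempting but not supported:

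- *The draw works only with exactly 108 eligible.* With more, intake can stop at 108. The gap concerns a shortfall only.
- *Atopy is the main risk factor.* The protocol names it as one of two potential confounders, and it excludes subjects with a history of dermatitis.
- *Time or weather is left unbalanced.* The background mentions "numerous factors including weather and baseline reactivity to substances that impact dermatitis" when discussing earlier studies. If the cohort is drawn at once there is no sequence to block, and the protocol does not establish rolling allocation.
- *The comparison is biased.* The allocation remains random, so any imbalance is due to chance.

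**Conclusion.** The point holds as a design weakness that should be corrected before allocation. Three parts rest on the text alone: the draw is tied to 108 numbers with no rule for a shortfall, the rounds are miscounted, and two confounders that the protocol itself names are not balanced although they are known in time.

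The size of the problem rests on two assumptions. For arm size it is the number eligible: no risk of an arm starting below 15 at 105 or more, a small one at 102 (4%), and a serious one by 96 (about 60%), if empty numbers fall at random. For atopy it is the prevalence: at 20-40% the mean gap between extreme arms is 4.3 to 5.2 of 18, and it reaches 5 or more in 42-64% of draws. The consequence is a less secure comparison of dermatitis proportions and thin strata in the planned stratified results, not an invalid trial.

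**What to change.** 1. State that 108 is the number randomised, not the number consented, and what is done if fewer are eligible when recruitment closes.
2. Replace the rounds of 18 with one computer-generated allocation of the confirmed-eligible cohort by the same independent researcher: sort by history of atopy, then deal in randomly permuted sets of six that run on across the two strata. Arm totals and atopic counts then each differ by at most one, whatever the number eligible (16 per arm at 96). Gender can be a second sort key, with looser balance. Because everything is allocated in one pass, no assignment can be guessed from earlier ones.
3. If subjects must be randomised as they become eligible, use permuted blocks stratified by atopy, with concealed and varying block sizes. Fixed blocks of six would be partly guessable by the coordinator, who is present both at consent and when materials are handed out. Arm totals may then differ slightly more, because each stratum can end in an incomplete block.

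The cost is a revised paragraph, a new list and a little more work for the researcher. No subjects, visits or procedures are added.

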*Randomization*: Subjects will be randomized into one of the six treatment groups using a computer-generated randomization list prepared by a researcher not involved in the running of the trial.

[figure not shown]

*Fig 1. Treatment Groups*

*Intervention*: At the beginning of the intervention subjects will be given a drawstring bag containing handwashing materials and hypoallergenic hygiene items including shampoo, conditioner, soap, and fragrance-free Vaseline along with instructions for use (Appendix G). Subjects will be asked to use the provided hygiene items in lieu of their usual products in order to control for possible other causes of skin irritation for the duration of the experiment. Subjects will be told that they can moisturize using the Vaseline as much as they would like. Vaseline is the best choice for this purpose because it is hypoallergenic, consistent with the way that healthcare workers commonly manage any skin itchiness and dryness, and consistent with available options for moisturizing in both the United States and West Africa. During the four weeks of intervention, subjects will be asked to wash their hands 10 times daily with the substance assigned to their treatment group, and instructed to use the soap provided in the hygiene kit for any hand or body washing they may do above and beyond the handwashing with their assigned substance (instructions in Appendix H). Each evening subjects will be asked to report to Anderson Hall on the Tufts Medford campus to pick up a refill of their assigned handwashing materials. Refills of the hygiene items will be available as needed. During the pickup time each day, subjects will also answer a brief questionnaire administered on tablets assessing adherence to the handwashing protocol, self-assessment of hand feel (including itchiness, pain, redness, flaking, cracks, skin thickening or swelling), receive a brief physical hand examination from study personnel, and take photos of both sides of each hand (Appendix I). The photos and hand exam scores will be reviewed daily for signs of dermatitis or skin abnormalities, and any suspected cases will be referred to [name] for treatment and assessment to determine whether continuation in the study is recommended. Dermatitis will be assessed using the HECSI scale, and the severity of the score will be used to guide the most likely course of action as described in Table 2 below.

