Data collection forms will be reviewed on a daily basis for completeness and to quickly identify major errors. [name] will review HECSI scores and photos of hands to identify any subjects that may be in need of follow up. Compliance with the study intervention will be measured by self-report in the daily questionnaire and by observation of the amount of handwashing substance left by each subject on a daily basis.

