[name] (Research Coordinator, Tufts PhD student) will be present during consent, baseline, and endline assessments, and daily administration of handwashing materials and surveys during the intervention along with [name] (Tufts Undergraduate Student) as an assistant. [name] will be working from the Tufts Medford campus for the duration of the study.

1. **Primary responsibility for the following activities**:
   - 1. **Obtaining informed consent**: [name] (Research Coordinator, Tufts PhD student) will be responsible for obtaining informed consent and will be assisted by other Tufts graduate and undergraduate students.
     2. **Providing on-going information to the study sponsor and the IRB**: [name] will be responsible for providing ongoing information to the study sponsor (USAID/OFDA) and the IRB and will be assisted by the research coordinator, [name].
     3. **Maintaining participant's research records**: [name] (Research Coordinator, Tufts PhD student) will be responsible for maintaining security and confidentiality of participant’s research records.
2. **Subject fees**: There are no fees associated with participation in this study. Travel costs associated with normal study activities will not be reimbursed, however in the case of an adverse event, transportation for medical consultation with [name].
3. **Study results**: Study results will not be disseminated directly to subjects, however subjects will be asked if they would like to be notified when results are published.
4. **Procedures to protect subject confidentiality**: Although this study presents a low risk of breach of confidentiality, procedures will be put in place to protect participant identity and associated information. Data is collected for research purposes only. Data (including photos of subject’s hands) will be password-protected and anonymized for analysis and identifying characteristics recorded will be minimized and used only for logistical purpose during the intervention stage of the study. Information will not be given without a subject’s consent. Photos will be used internally to assess hand health and confirm accuracy of data and will not be shared without permission from subjects. Photos will be stored for one year after the end of the intervention period and then destroyed. Any Adverse Event reports will include only subject ID numbers without any identifying information.
5. **Confidentiality**:

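### Blinded HECSI scoring is promised, but the daily hand exam is placed at product pickup with no stated separation of examiner from product

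*Protocol*

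**What the plan says.** The Blinding paragraph, under Sample size and statistical analysis, makes the commitment: "Researchers assessing HECSI scores for the hand exam and applying and interpreting results of the patch testing will be blinded to subject treatment group". It supports this with two measures: "Daily surveys will not record treatment arm and subjects will be instructed not to identify their group to examiners". The same paragraph explains that subjects cannot be blinded because soap, sanitizer and chlorine are plainly different, and that subjects on chlorine are not told which of the four solutions they have.

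Under Experimental design, Intervention, subjects come to one building each evening "to pick up a refill of their assigned handwashing materials". The assessment belongs to that visit: "During the pickup time each day, subjects will also answer a brief questionnaire administered on tablets", and they "receive a brief physical hand examination from study personnel". For each intervention week, the Subject Timeline has subjects collect materials and "answer a short survey about compliance and hand feel, including a hand exam and photos of hands".

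The Data Collection text says that compliance is measured by self-report and "by observation of the amount of handwashing substance left by each subject on a daily basis".

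Under Subject Participation, the research coordinator "will be present during consent, baseline, and endline assessments, and daily administration of handwashing materials and surveys during the intervention along with" an undergraduate assistant. The clinical co-PI attends only some of the hand exams and is based at another institution.

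**The concern.** HECSI is a graded visual score, and the Data Analysis paragraph makes it the reference measure of clinical dermatitis within the primary outcome. The other measure, self-perception, comes from subjects who know their product class. HECSI is therefore the one outcome measure on which blinding across classes is possible, and the Blinding paragraph relies on it.

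The described visit brings the examiner close to the one thing that identifies the class. If the person scoring hands sees a refill handed over or a remainder checked, doubtful erythema or scaling may be graded with the product in mind. That is detection bias in comparing chlorine with soap and with sanitizer, which is central to the stated aim. It could recur at each daily exam and could not be corrected after data collection.

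**Working it through.** There is no figure in the plan to reproduce. The check sets the promise beside the procedure.

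1. **What the promise requires.** The HECSI examiner must not learn the arm by any route: written record, spoken disclosure or sight of the product.

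2. **What the safeguards cover.** Leaving the arm off the survey covers the written record. Instructing subjects covers speech. Nothing stated covers sight.

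3. **Whether sight reveals the arm.** By the Blinding paragraph's own account, the three product classes are readily told apart. Seeing the product reveals soap, sanitizer or chlorine. It need not reveal which chlorine solution, unless the examiner also knows the dispensing list.

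4. **Whether the examiner is in a position to see it.**
   - Place and time: the exam is part of the pickup visit (Intervention; Subject Timeline).
   - People: the examiner is described only as study personnel. The staff named for daily dispensing and surveys are the coordinator and one assistant, and the Subject Timeline describes the survey as including the hand exam. Read together, these passages allow the dispenser and the examiner to be the same person.
   - Further contact: leftover product is inspected daily and, in the first intervention week, subjects receive an orientation specific to their group. The protocol does not say who does either.

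5. **What separation is stated.** Only the researcher who randomizes is kept apart from subjects. No section separates examiner from dispenser by person, room or order of events, and none describes coded or opaque containers.

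6. **Which comparisons are exposed.** Six arms give 6 × 5 / 2 = 15 pairwise comparisons. The four chlorine arms give 4 × 3 / 2 = 6 among themselves. The remaining 15 − 6 = 9 cross product classes: 4 of chlorine with soap, 4 of chlorine with sanitizer, and 1 of soap with sanitizer. Those 9 lose protection if the class is seen; the other 6 may keep it.

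**The case against.** The strongest reply is that the protocol does commit to blinded examiners and nowhere says that the person who dispenses also scores hands. The personnel section states who is present at dispensing and surveys, and mentions hand exams separately for the clinical co-PI. Other graduate and undergraduate students help with consent and survey work, so the team may exceed two. A separate examiner is neither described nor ruled out. This stands: a reader might infer that blinding is broken, but the text shows only that it is unprotected.

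Four further readings go beyond the documents:

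- **Leftovers returned in front of the examiner.** The protocol says the remaining amount is observed daily, not where, by whom or at what point in the visit.
- **Bias against chlorine.** The hypothesis is non-directional. The background attaches dermatitis concerns to soap and sanitizer as well, and says the risk has not been shown for NaDCC.
- **A computed effect on the results.** One could count how many subjects of 15 would move an arm to the 20% that the protocol treats as problematic. But the protocol fixes no HECSI score that makes a subject a case and gives no misclassification rate, so such a count would only be illustrative.
- **The same fault in patch testing.** Baseline patches precede randomization, every subject is patched with all six substances, and the Day 7 endline reading falls after the daily pickups end. Earlier knowledge of the product could carry over, but the pickup argument does not extend to that reading.

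Daily photographs are also a partial resource: they are reviewed for follow-up and used to confirm data accuracy. The protocol does not describe them as an independent blinded scoring, so they do not fill the gap.

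**Conclusion.** The concern holds as a conflict between a stated protection and the procedure meant to deliver it. It is more than missing detail, because the protocol itself places the exam at the pickup of a recognisable product, describes the survey run by the dispensing staff as including that exam, and offers safeguards against written and spoken disclosure only.

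Blinding of HECSI across soap, sanitizer and chlorine is not secured, which affects 9 of the 15 pairwise comparisons. Masking among the four chlorine solutions may survive. The size and direction of any bias cannot be derived from the protocol.

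This rests on two assumptions: that no separate examiner is specified in material not shown, such as an appendix or procedure manual, and that refills are visible when handed over, since no concealed packaging is described. If either is wrong, the remedy is only to say so in the protocol. The change should be made before the intervention starts.

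**What to change.** Reconcile the Blinding paragraph, the Intervention text, the Subject Timeline, the Data Collection text and the personnel section by stating that:

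- the person who scores HECSI takes no part in dispensing, leftover checks or arm-specific orientation;
- at each evening visit the hand exam comes first, in a separate room or behind a screen, out of sight of any product;
- refills and returned containers are in opaque bags labelled by subject ID only, packed by someone who does not score hands.

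The packer should not be the researcher who prepares the randomization list, because the Randomization text says that researcher is not involved in running the trial.

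The two named daily staff can cover this: one examines only, while the other packs, dispenses, checks leftovers and gives the orientation. This assumes both attend each evening; a stand-in must keep to the same split. The cost is a slightly longer visit and opaque packaging, with no change to sample size, outcome or schedule.
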